### 2.11. Sample Size and Recruitment

Based on similar studies conducted primarily in pediatric populations, but also in adults [11,12], and taking into account the multiple outcomes to be obtained from the analysis of multiple variables, we estimate that, to achieve a significance level of 0.05 and a statistical power (β) of 0.8, a sample size of 48 patients per group would be required. Adjusting for a 5% dropout rate, we plan to recruit at least 50–55 patients per group to ensure the robustness of the analysis.

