#### 2.13.3. Characterization of Quantifiable Analytical Parameters in Serum, Urine, and Stool

The following hematological, biochemical, metabolic, nutritional, and inflammatory parameters will be quantified in serum:Hematological and coagulation parameters: complete blood count (CBC) and coagulation profile.General biochemical profile: fasting glucose, electrolytes (sodium, potassium, chloride), nitrogenous compounds (urea, creatinine), mineral metabolism markers (calcium, phosphorus, magnesium), hepatic function enzymes (aspartate aminotransferase [AST/GOT], alanine aminotransferase [ALT/GPT], gamma-glutamyl transferase [GGT], alkaline phosphatase, total and direct bilirubin, lactate dehydrogenase [LDH], creatine kinase).Metabolic and endocrine markers: insulin, homeostatic model assessment for insulin resistance (HOMA-IR), C-peptide, and glycated hemoglobin (HbA1c).Lipid profile: total cholesterol, high-density lipoprotein cholesterol (HDL-C), low-density lipoprotein cholesterol (LDL-C), and triglycerides.Nutritional biomarkers: prealbumin, albumin, fat-soluble vitamins (A, D, E), trace elements (zinc, selenium), vitamin B12, iron, folate, ferritin, transferrin, and transferrin saturation index.Inflammatory biomarkers: C-reactive protein (CRP), erythrocyte sedimentation rate (ESR), and interleukin-6 (IL-6). Inflammatory markers will be quantified using high-sensitivity multiplex immunoassays to enhance precision and reduce inter-assay variability.

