Analysis in fecal samples will include the following:Fecal calprotectin: a surrogate marker of intestinal inflammation, measured using enzyme-linked immunosorbent assay (ELISA) or equivalent high-sensitivity immunoassays.Analysis of the gut microbiota composition will be performed by 16S rRNA gene sequencing in stools. DNA extraction from stool samples will be performed using 200 mg of sample using the QIAamp DNA Stool Mini kit (Qiagen, Manchester, UK), following the manufacturer’s instructions. The concentration and quality of the DNA will be determined by the Agilent 2200 TapeStation system. To create the libraries, DNA samples (5 ng/µL) will be amplified using a primer, encoding the hypervariable regions V2-4-8 and V3-6, 7-9 of the bacterial 16S rRNA using the 16S Metagenomics Kit (Thermo Fisher, Waltham, MA, USA). The amplicons obtained will be purified using AMPure^®^ XP beads (Beckman Coulter, Pasadena, CA, USA) and, subsequently, the libraries will be created using the Ion Plus Fragment Library kit (Thermo Fisher, Waltham, MA, USA) and the Ion Xpress Barcode Adapters 1–16 kit (Thermo Fisher, Waltham, MA, USA) to add barcodes to purified amplicons. The libraries will be purified using AMPure^®^ XP beads (Beckman Coulter, Pasadena, CA, USA) and quantified by fluorescence. Sequencing of the libraries will be carried out using an Ion S5 platform. The results of composition, diversity, and richness will be analyzed using the QIIME2 platform, and functionality will be analyzed through the PICRUST software package (Version v2.6.2).

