### 2.15. Statistical Methods

All statistical analyses will be performed using SPSS software version 22.0, considering *p* < 0.05 as the threshold for statistical significance. A descriptive analysis of the variables will be conducted, providing point estimates and 95% confidence intervals. Continuous variables will be expressed as means and standard deviations or medians depending on the distribution of the data. Categorical variables will be reported as frequencies and percentages.

Comparisons of continuous variables will be performed using Student’s *t*-test (for two-group comparisons) or ANOVA (for comparisons involving more than two groups). Associations between categorical variables will be assessed using the chi-square test. Correlation analyses will be conducted using Pearson’s or Spearman’s correlation coefficients, depending on the normality of the variables under study. Relationships between multiple variables will be analyzed using multivariate statistical models.

Given the multiple outcomes to be assessed and the multiple comparisons to be analyzed, a Bonferroni correction (0.05/no. of comparisons as the significance level) will be also performed to avoid the risk of false positives.

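### Section 2.15 fixes single-step Bonferroni, a valid but needlessly conservative rule; Holm's step-down procedure gives the same familywise control with equal or better power at no cost in data

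*Protocol article*

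**What the plan says.** Section 2.15 first sets p < 0.05 "as the threshold for statistical significance" for all analyses. It then adds, "Given the multiple outcomes to be assessed and the multiple comparisons to be analyzed", that "a Bonferroni correction (0.05/no. of comparisons as the significance level) will be also performed to avoid the risk of false positives". This is single-step Bonferroni: every p-value is compared with the same cut-off, 0.05 divided by the number of comparisons. No other procedure is named.

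Section 2.11 sizes the trial "to achieve a significance level of 0.05 and a statistical power (β) of 0.8" and concludes that "a sample size of 48 patients per group would be required". The basis is given only as "Based on similar studies conducted primarily in pediatric populations, but also in adults", with no effect size, standard deviation or event rate.

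Section 2.13.3 shows how many outcomes there could be. Under the sentence "The following hematological, biochemical, metabolic, nutritional, and inflammatory parameters will be quantified in serum" it lists a long laboratory panel, and for the stool sequencing it says that "The results of composition, diversity, and richness will be analyzed using the QIIME2 platform".

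**The concern.** Once a plan commits to familywise control at 0.05, the remaining choice is how efficiently to achieve it. Single-step Bonferroni holds every test to the strictest cut-off, even after some hypotheses have been rejected. Holm relaxes the cut-off one step after each rejection and keeps the same guarantee without any assumption on how the outcomes are correlated. A plan that fixes Bonferroni therefore gives up some power for no added protection.

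What is at stake is a modest number of true effects in small families of outcomes. The abstract expects the diet to improve body composition, remission, inflammatory markers, microbiota and quality of life together. That is the setting in which Holm gains most. Section 3 also acknowledges that the sample size is limited, so power that can be had for free is worth taking.

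**Working it through.** **Inputs from the protocol.** 48 per group, significance level 0.05 and power 0.8 (2.11); 1:1 allocation (2.12); cut-off 0.05/m for m comparisons (2.15).

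**Assumed, because the protocol does not state them.** Two-sided tests; m = 10 as a small family; the effect size; the number of real effects; correlation 0 or 0.3 between outcomes.

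**Step 1: the effect that 48 per group corresponds to.** The figure of 48 cannot be reproduced from stated inputs, because no effect size is given. Turning it round with the normal approximation:

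d = (1.960 + 0.842) × √(2/48) = 2.802 × 0.204 = 0.572.

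With the t distribution it is 0.578. These are the effects used below.

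**Step 2: what Bonferroni costs at that effect.** Power per test = Φ(d√(n/2) − z), where d√(n/2) = 0.572 × √24 = 2.802 and z is the two-sided critical value at 0.05/m.
- m = 1: Φ(2.802 − 1.960) = 0.80
- m = 10: Φ(2.802 − 2.807) = 0.50
- m = 45: Φ(2.802 − 3.261) = 0.32

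**Step 3: the two rules side by side, m = 10.** Bonferroni compares all ten p-values with 0.05/10 = 0.005. Holm orders them, compares the smallest with 0.05/10 = 0.005, the next with 0.05/9 = 0.0056, the next with 0.05/8 = 0.00625, and so on up to 0.05/1, and stops at the first failure. No Holm cut-off lies below 0.005, so every Bonferroni rejection is also a Holm rejection.

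**Step 4: size of the gain, small family.** Simulated t-tests, 48 per arm, ten outcomes, d = 0.578, average power over the real effects:

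| Real effects out of ten | Bonferroni | Holm | Gain |
|---|---|---|---|
| 10 | 49% | 60% | 11 points |
| 6 | 48% | 53% | 5 points |
| 3 | 49% | 50% | 1 to 2 points |

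Holm's familywise error was at most 0.047 in repeated runs.

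**Step 5: size of the gain, large family.** Section 2.13.3 names 17 biochemistry + 4 endocrine + 4 lipid + 13 nutritional + 3 inflammatory analytes + calprotectin = 42, before blood-count and coagulation items. Simulations with m = 45 and m = 200, with 10% to 50% of effects real and independent tests, give:
- d = 0.572, m = 45: Bonferroni 0.32 to 0.33, Holm 0.32 to 0.34
- d = 0.572, m = 200: both about 0.20
- d = 0.8, m = 45: 0.75 against 0.75 to 0.79
- d = 0.8, m = 200: 0.60 against 0.61 to 0.64

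So Holm adds 0 to 2 points at the moderate effect, and about 4 points at most at the larger one. Familywise error reached at most 0.051 for Holm, which is within simulation error (√(0.05 × 0.95/4000) = 0.003).

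**The case against.** **Bonferroni is valid, so this is a preference.** The first half stands. Bonferroni holds under any dependence and serves the stated purpose of limiting false positives. But preferring Holm is not a matter of taste: it gives the same guarantee and never rejects less. Nor is the procedure left open for a statistical analysis plan, because 2.15 names it.

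**The gain is small.** This largely stands. Eleven points need every outcome in a small family to be real; with six of ten it is about 5 points, and in large families it nearly vanishes. Holm would not restore 80% power.

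**Holm has a downside.** This stands, to a small extent. Bonferroni has simple matching simultaneous confidence intervals and Holm does not. Section 2.15 promises 95% intervals in the descriptive analysis, but not simultaneous ones.

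**A reader might infer that Bonferroni discards most of the true laboratory and microbiota effects that false-discovery-rate control would find.** The documents do not support this.
- Relative to Benjamini-Hochberg, Bonferroni loses about 27% to 45% of detected effects for 42 analytes at assumed effects, and about 31% for an assumed 150 taxa. The loss clearly passes half only when very many tests at moderate effects are pooled, such as 200 tests at d = 0.572 (51% to 70%).
- Benjamini-Hochberg controls a different, weaker error. The chance of at least one false positive becomes about 12% to 23% at 42 analytes and 46% at 150 taxa. That is a trade-off for the investigators.
- Section 2.13.3 describes composition, diversity and richness. It does not state per-taxon testing.

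**A reader might also infer that the laboratory and microbiota aims would come out negative because of the correction.** This is not shown. By its own wording, 2.15 applies Bonferroni in addition to the p < 0.05 threshold, so unadjusted results are planned as well.

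**Conclusion.** The point holds as an efficiency improvement, not as an error of validity. Single-step Bonferroni is the only correction that 2.15 names, and Holm dominates it as a testing rule. The benefit ranges from 1 to 2 points of average power (three of ten effects real) to about 11 points (all ten real) at d = 0.58 with 48 per group. It is about 0 to 2 points in families of 40 or more tests at that effect.

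That Holm is never worse rests on no assumption. The sizes rest on the assumed family size, effect size, number of real effects and two-sided testing, none of which the protocol gives. Using false-discovery-rate control for the laboratory panel or any per-taxon tests is a separate, optional choice and not part of this conclusion.

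**What to change.** In 2.15, replace the Bonferroni correction at 0.05 divided by the number of comparisons with the Holm step-down procedure at a familywise level of 0.05, over the same comparisons.

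The cost is one sentence, changed before outcome data are seen, with no extra patients, samples or measurements. The only thing given up is Bonferroni's simple simultaneous confidence intervals; the 95% intervals already planned are unaffected.

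Optionally, the investigators may choose Benjamini-Hochberg at 5% for the laboratory panel and for any per-taxon tests. If so, 2.15 should say that for those results the controlled error is the expected share of false findings, not the chance of any false finding.

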## 3. Discussion

The findings of this study could contribute to the implementation of nutritional therapy in adult patients with active luminal CD (non-stricturing, non-penetrating) of the small intestine, with or without colonic involvement, who are initiating treatment with biologic agents or JAK inhibitors. Partial enteral nutrition (PEN) combined with the exclusion diet (ED) has demonstrated efficacy in inducing remission in both pediatric and adult patients, promoting mucosal healing and serving as a rescue therapy for patients who fail biologic therapy [11,12].

In this context, the Crohn’s Disease Exclusion Diet (CDED) has emerged as a promising whole-food-based dietary intervention, specifically designed to reduce exposure to dietary components that impair the intestinal barrier and alter the gut microbiome. In a pivotal 12-week prospective randomized trial, Levine et al. compared CDED combined with partial enteral nutrition (PEN) to exclusive enteral nutrition (EEN) in children with mild to moderate CD [12]. The study showed that CDED + PEN was significantly better tolerated than EEN (97.5% vs. 73.6%, *p* = 0.002), and while both approaches achieved comparable remission rates at week 6, sustained corticosteroid-free remission at week 12 was notably higher in the CDED + PEN group (75.6% vs. 45.1%, *p* = 0.01) [14]. Additionally, the CDED + PEN group exhibited sustained reductions in inflammatory biomarkers and favorable modulation of the fecal microbiota [12]. These findings support the clinical utility of CDED + PEN as a more tolerable and effective strategy for inducing and maintaining remission in pediatric CD. Recent clinical data on adult patients reinforce the efficacy of CDED beyond pediatric populations. In a study involving 32 participants (18 women and 14 men), clinical remission was achieved in 76.7% of patients at 6 weeks and in 82.1% at 12 weeks of therapy [11]. Furthermore, fecal calprotectin levels showed a significant reduction by the second follow-up time point compared with baseline (*p* = 0.021) [11]. These findings suggest that CDED is also an effective therapeutic option for inducing remission in adult patients with CD.

The primary advantage of this dietary strategy lies in its balanced, sustainable, and palatable nature, making it easier to adhere to over time. This is largely due to its inclusion of dietary fiber and essential substrates necessary for the production of short-chain fatty acids [10]. The exclusion diet is based on the elimination or inclusion of specific dietary components while ensuring a nutrient composition that supports the growth and maintenance of lean body mass [15,16].

Foods and additives that should be excluded from this diet include those associated with high fat intake (particularly from animal sources, such as red meat), dairy products, wheat, alcohol, yeast, and insoluble fiber [16]. Additionally, food additives recommended for avoidance include emulsifiers, carrageenan, maltodextrins, sulfites, and titanium dioxide [16]. Conversely, the diet should be low in taurine, rich in proteins and complex carbohydrates, and free of gluten or modified starches [15]. Thus, the CDED consists of a series of obligatory, permitted, and prohibited foods that can be eaten at different phases of the diet as detailed in Table 2.

On the other hand, the available evidence regarding the impact of CD on body composition remains scarce and heterogeneous, highlighting the need for further high-quality research and data publications [12,13,17,18]. These findings could represent an opportunity to enhance the management of CD and integrate body composi-tion assessment into routine clinical practice. The effect of the exclusion diet on muscle quantity, quality, and functionality may be related to the patient’s quality of life, and its monitoring and follow-up is a guiding parameter in nutritional intervention by in-creasing the intake of certain macronutrients (such as protein). Information on body composition would allow the personalization of nutritional intervention.

This study presents some methodological limitations. First, the use of self-administered dietary assessment tools (PREDIMED and FFQ) introduces inherent biases, including recall bias and social desirability bias, which may compromise the accuracy of reported dietary adherence. Second, inter-individual variability in adherence to the nutritional intervention could affect the interpretation of objective outcome measures. Additionally, attrition and a relatively limited sample size may reduce the statistical power of the study, potentially limiting the ability to detect clinically meaningful differences or perform robust subgroup analyses. Residual confounding variables—such as psychological stress, levels of physical activity, and other lifestyle factors—may also influence study outcomes despite attempts at control. Finally, both inter- and intra-observer variability in ultrasound assessments, including intestinal ultrasound and quadriceps rectus femoris muscle evaluation, constitute further sources of potential measurement bias.

## Figures and Tables

**Figure 1 jcm-14-03998-f001:**
[figure not shown]
Flowchart of the trial intervention.

**Figure 2 jcm-14-03998-f002:**
[figure not shown]
Questionnaire of quality of life (CVEII-9).

**Figure 3 jcm-14-03998-f003:**
[figure not shown]
International physical activity questionnaire (IPAQ).

**Figure 4 jcm-14-03998-f004:**
[figure not shown]
Mediterranean diet adherence questionnaire (PREDIMED).

**Table 1 jcm-14-03998-t001:** Proposal for the follow-up of adult Crohn’s disease patients included in this study.

Study Period						
Timepoint	Pre-DE	t0	t1 (6 w)	t2 (12 w)	t3 (24 w)	t4 (48 w)
**Enrollment**						
Diagnosis (Index, Harvey–Bradshaw Index, MUST)	X					
Inclusion criteria and exclusion criteria	X					
Informed consent signature	X					
**Intervention**						
Standard nutritional recommendations vs. ED + enteral nutrition		X	X	X	X	X
**Assessments**						
Quality of life questionnaire (CVEII-9)		X	X	X	X	X
Harvey–Bradshaw activity index		X	X	X	X	X
Physical activity questionnaire (PAQ)		X			X	X
Food Frequency Questionnaire (FFQ)		X			X	X
24 h dietary recall		X	X	X	X	X
Mediterranean diet adherence questionnaire (PREDIMED)			X		X	X
Anthropometry (weight, height, BMI)		X		X	X	X
Sarcopenia screening (SARC-F)		X		X	X	X
Functional sarcopenia tests (dynamometry)		X		X	X	X
Bioelectrical Impedance Analysis (BIA)		X	X	X	X	X
Nutritional ultrasound		X		X	X	X
Blood tests, urine and stool samples		X	X	X	X	X
Intestinal imaging (MRI/intestinal ultrasound).		X			X	X
Intestinal biopsy. Optional.		X			X	X

Pre-DE: before diet exclusion. t0: baseline or initial visit. t1 (6 w): visit at 6 weeks. t2 (12 w): visit at 6 weeks. t3 (24 w): visit at 24 weeks. t4 (48 w): visit at 48 weeks.

**Table 2 jcm-14-03998-t002:** Obligatory, permitted, and prohibited foods in the exclusion diet in patients with Crohn’s disease.

Phase	Type of Food	
Phase 1 (0–6 weeks)	Obligatory	Protein-rich foods: fresh chicken breast (at least 150–200 g/day), 2 eggs/day. Carbohydrate-rich foods: 2 fresh potatoes/day peeled, cooked and cooled before consumption, 2 bananas/day, 1 apple/day peeled.
	Permitted	Protein-rich foods: 100–150 g of fresh white fish once a week as a substitute for chicken. Carbohydrate-rich foods: white rice (unlimited), rice noodles without preservatives (unlimited), rice flour for baking (unlimited). Fruits: 1 avocado/day (no more 1/2 avocado per meal), 5 ripe strawberries/day, 1 cantaloupe slice/day. Vegetables: 2 tomatoes/day (or 6 cherry tomatoes), 2 cucumbers/day peeled, 1 carrot/day, fresh spinach (225 g raw leaves/day), 3 lettuce leaves once a day. Condiments: olive oil, canola oil, salt, pepper, paprika, cinnamon, cumin, turmeric, mint, oregano, coriander, rosemary, sage, basil, thyme, dill, parsley, onion (all types), garlic, ginger, natural lemon juice, honey (3 tbsp/day), sugar (3 teaspoons/day). Drinks: water, sparkling water, infusions, 1 glass of freshly squeezed orange juice per day.
	Prohibited	Protein-rich foods: pre-cooked or smoked processed meat and fish, seafood, red meat, pork, pork, turkey, and other poultry parts, soy products, dairy products, ice cream, vegetable milks (soy, rice, almond). Carbohydrate-rich foods: wheat products (breakfast cereals, bread and baked goods of any kind), baker’s yeast and other flours, gluten-free products not mentioned above, soya products, pulses (lentils, peas, chickpeas and beans), maize, frozen potatoes. Fruits: dried fruits, all other fruits. Vegetables: frozen vegetables, kale, leek, asparagus, artichokes, all other vegetables not mentioned as permitted. Condiments: margarine, sauces, salad dressings, syrups (maple syrup, corn syrup, etc.), jam of any kind, artificial sweeteners, spice mixtures, other oils (soybean oil, sunflower oil, corn oil, etc.), marmalade of any kind, artificial sweeteners and oil spray. Beverages: soft drinks, fruit juice, other sweetened beverages, alcoholic beverages, coffee, chocolate milk, milkshakes, all types of tea (leaf and tea bags). Nuts and dried fruit. Others: canned goods, packaged snacks (crisps, crackers, popcorn, etc.), candy, chocolate, cakes, biscuits, chewing gum. Foods that are not on the list of recommended or permitted foods are prohibited.
Phase 2 (7–12 weeks)	Obligatory	Same as phase 1.
	Permitted	Protein-rich foods: 100–150 g of fresh white fish once a week as a substitute for chicken, one can of tuna in olive or canola oil once a week. Eating red meat is not recommended, but if you wish, you should limit yourself to a fresh fillet of unprocessed lean meat, up to 200 g per week (only once a week). Carbohydrate-rich foods: white rice (unlimited), rice noodles without preservatives (unlimited), rice flour for baking (unlimited), ½ sweet potato/day, bread 1 slice/day (preferably homemade), lentils, peas, chickpeas or dried beans, half a cup/day uncooked, quinoa (unlimited), 50 g oats (one serving of oatmeal or crackers is allowed 1 or 2 times a day). Fruits: 1 avocado/day (no more 1/2 avocado per meal), 5 ripe strawberries/day, 1 cantaloupe slice/day, one pear, peach or kiwi fruit per day, 10 blueberries (25 g) can replace the allowed strawberries. From week 10 onwards, all fruits can be introduced in small quantities (except those on the off-limits list). Vegetables: 2 tomatoes/day (or 6 cherry tomatoes), 2 cucumbers/day peeled, 1 carrot/day, fresh spinach (225 g raw leaves/day), 3 lettuce leaves once a day, courgette (1 large or 2 small), 4–6 fresh mushrooms, 2 broccoli or cauliflower florets (but not all at the same time). From week 10 onwards, all vegetables can be introduced in small quantities (except those on the off-limits list). Condiments: olive oil, canola oil, salt, pepper, paprika, cinnamon, cumin, turmeric, mint, oregano, coriander, rosemary, sage, basil, thyme, dill, parsley, onion (all types), garlic, ginger, natural lemon juice, honey (3 tbsp/day), sugar (3 teaspoons/day), baking soda or baking powder. Drinks: water, sparkling water, infusions, 1 glass of freshly squeezed orange juice per day, chamomile tea (permitted from week 7 onwards). Nuts: unsalted, unroasted, and unprocessed almonds or walnuts, 36 g/day Tahini (without emulsifiers and sulfites).
	Prohibited	Protein-rich foods: pre-cooked or smoked processed meat and fish, seafood, red meat, pork, pork, turkey, and other poultry parts, soy products, dairy products, ice cream, vegetable milks (soy, rice, almond). Carbohydrate-rich foods: wheat products (breakfast cereals, bread and baked goods of any kind), baker’s yeast and other flours, gluten-free products not mentioned above, soya products, pulses (lentils, peas, chickpeas and beans), maize ((permitted from week 10), frozen potatoes. Fruits: dried fruits, all other fruits (permitted from week 10 onwards). Fruit is not permitted under any circumstances: persimmon, passion fruit, pomegranate, prickly pear. Vegetables: frozen vegetables, kale, leek, asparagus, artichokes. Condiments: margarine, sauces, salad dressings, syrups (maple syrup, corn syrup, etc.), jam of any kind, artificial sweeteners, spice mixtures, other oils (soybean oil, sunflower oil, corn oil, etc.), marmalade of any kind, artificial sweeteners and oil spray. Beverages: soft drinks, fruit juice, other sweetened beverages, alcoholic beverages, coffee, chocolate milk, milkshakes, all types of tea (leaf and tea bags). Nuts and dried fruit. Others: canned goods, packaged snacks (crisps, crackers, popcorn, etc.), candy, chocolate, cakes, biscuits, chewing gum. Foods that are not on the list of recommended or permitted foods are prohibited.
Phase 3 (13 week)	Permitted	The phase 2 diet will be followed for 5 days of the week (Monday to Friday) with the following additions: Protein-rich foods: other parts of the chicken can be used, but the skin, wings, and offal should be avoided; fresh seafood, white fish or salmon, once a week, one serving per day of natural unprocessed yogurt with all-natural fat and no additives. Carbohydrate-rich foods: two slices of bread per day (preferably homemade), a small portion of pasta can be eaten instead of bread (200 g cooked). Fruits: all fruits and berries, including dehydrated fruits if they are sulfite-free, except for fruits that are expressly not allowed. Vegetables: all vegetables except those expressly not allowed (provided you do not suffer from stenosis). Drinks: one cup of black coffee or tea (no instant coffee or capsules and only 1 cup per day). Same restrictions for other foods, beverages, and condiments as in phase 2. Weekends (Saturdays and Sundays): foods that are not included in the ED are allowed at free meals. It is important not to overeat foods that are not included in the ED. Try to maintain a varied diet also during free meals at weekends. Homemade food is preferable to frozen or processed food. One free home-cooked breakfast and one free home-cooked meal (lunch or dinner) per day on Saturdays and Sundays (including wheat, dairy, fish and other types of meat).
	Prohibited	Protein-rich foods: frozen doughs (cake or pizza bases), processed meats (such as hot dogs, sausages, bacon), ready meals (frozen from fresh produce), and soft drinks. Fruits: passion fruit, persimmon, prickly pear, pomegranate. Vegetables: raw celery, large quantities of kale, leeks.

